## Abstract

**Background:**

Low Back Pain is a major public health problem all over the western world. Active approaches including exercise in the treatment of low back pain results in better outcomes for patients, but it is not known exactly which types of back exercises are most beneficial or whether general physical activity provide similar benefits.

Nordic Walking is a popular and fast growing type of exercise in Northern Europe. Initial studies have demonstrated that persons performing Nordic Walking are able to exercise longer and harder compared to normal walking thereby increasing their cardiovascular metabolism. Until now no studies have been performed to investigate whether Nordic Walking has beneficial effects in relation to low back pain.

The primary aim of this study is to investigate whether supervised Nordic Walking can reduce pain and improve function in a population of chronic low back pain patients when compared to unsupervised Nordic Walking and advice to stay active. In addition we investigate whether there is an increase in the cardiovascular metabolism in persons performing supervised Nordic Walking compared to persons who are advised to stay active. Finally, we investigate whether there is a difference in compliance between persons receiving supervised Nordic Walking and persons doing unsupervised Nordic Walking.

**Methods:**

One hundred and fifty patients with low back pain for at least eight weeks and referred to a specialized secondary sector outpatient back pain clinic are included in the study. After completion of the standard back centre treatment patients are randomized into one of three groups: A) Nordic Walking twice a week for eight weeks under supervision of a specially trained instructor; B) Unsupervised Nordic Walking for eight weeks after one training session with an instructor; C) A one hour motivational talk including advice to stay active. Outcome measures are pain, function, overall health, cardiovascular ability and activity level.

**Results:**

No results available at this point.

**Discussion:**

This study will investigate the effect of Nordic Walking on pain and function in a population of people with chronic LBP.

**Trial Registration:**

registration # NCT00209820

## Background

Low back pain (LBP) is a major public health problem all over the western world and one of the leading causes for sick leave and disability [1]. In Denmark, 35–50% of the adult population have suffered from LBP, in the last year, and 21% have had symptoms the past 14 days [2]. Therefore high quality research aiming at identifying effective treatment and prevention strategies is warranted.

Throughout the last three decades the management of LBP has changed radically from primarily passive treatments and bed rest to patient centred active treatments involving exercise, resulting in improved outcomes with regards to pain, daily function, and return to work [3-5]. As a result of this development, a wide variety of specific exercise regimes have emerged, however, there is little evidence that one type of exercise is superior to another in the treatment of LBP, even though sub-groups of patients benefiting from specific exercise interventions have been identified [5]. Based on results from a recent randomized clinical trial Hurwitz et al. went as far as to suggesting that maybe LBP patients should refrain from back specific exercises and instead focus on non-specific physical activities in order to reduce pain and improve health [6], thereby adding LBP to the already long list of health conditions that are influenced positively by physical activity.

Nordic Walking (NW) is a fast growing and popular way to exercise in northern Europe, in particular in Scandinavia and Germany [7]. NW is low-tech and cheap; it doesn't require a lot of skill and can be done by almost anybody. NW is performed by walking using poles with rubber or spike tips in the same way as in Nordic style skiing. By using the poles the muscles in the upper body are activated and the length of each step taken is increased resulting in a faster gait. Consequently, NW appears to increase cardiovascular metabolism even in healthy people [8,9]. So far the effect of NW on pain and disability in relation to LBP has not been investigated however if shown effective, NW would constitute an attractive low-tech, low-risk, and low-cost intervention. Furthermore, it is not known whether LBP patients are willing to comply with the prescribed dose and frequency, a problem commonly encountered in other forms of exercise therapy for LBP [10], and whether compliance plays a role in relation to pain and disability outcomes.

The primary aim of this single blind randomized clinical trial is therefore to compare the effect of supervised NW versus non-supervised NW versus information about the benefits of physical activity in relation to pain and pain related function using standardized outcome measures. Secondary objectives are 1) to compare the increase in cardiovascular metabolism between the supervised NW group and the information group and 2) to evaluate compliance to NW between the supervised and non-supervised NW group.

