### Outcome measures

#### Primary outcome measures

##### Low Back Pain Rating Scale

Low Back Pain Rating Scale was developed to measure the dimensions of pain, disability, and physical impairment for patients with LBP [11]. The pain assessment index is measures using three 11-box numeric rating scales (pain now, worst and average pain in the last two weeks) for back and leg pain separately. Each response scale score is added giving a scale range of 0–60 points. The disability index comprises 15 items scaled as yes = 0 points, can be a problem = 1 point, no = 2 points, giving a total of 0–30 points

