##### Patient Specific Function Scale

Patient Specific Function Scale was developed to assess functional limitations in a variety of clinical presentations. Patients are asked to identify three important activities with which they are having difficulty or are unable to perform because of their problem. In addition to specifying the activities, patients are asked to rate on an 11-box numeric rating scale the current level of difficulty associated with each activity [12]

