### Follow-up

Follow-up data are collected at eight weeks, six months and one year (Figure 1).

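### Three co-equal primary scores and two or three unranked group contrasts, while alpha 0.05 and N = 150 cover one two-group NRS comparison: no single primary hypothesis is named

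*Protocol article*

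**What the plan says.** **Scores.** Under Primary outcome measures the article places two instruments that yield three totals.
- LBPRS pain index: six 11-box scales, three for back and three for leg. "Each response scale score is added giving a scale range of 0–60 points".
- LBPRS disability index, scored separately from 0 to 30: "The disability index comprises 15 items".
- A second instrument under the same heading: "Patient Specific Function Scale was developed to assess functional limitations in a variety of clinical presentations".

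None is put ahead of the others.

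**Contrasts.** Call supervised walking A, unsupervised walking B and information C. The Background's primary aim is to "compare the effect of supervised NW versus non-supervised NW versus information about the benefits of physical activity". The Abstract asks whether supervised walking reduces pain and improves function "when compared to unsupervised Nordic Walking and advice to stay active". The first admits A v B, A v C and B v C; the second only the two contrasts that involve A. Neither ranks them.

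**Times.** "Follow-up data are collected at eight weeks, six months and one year". None is called primary.

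**Error rate and size.** Data analyses says that power rests on the primary outcome measures, in the plural. It then gives one calculation: 80% power, alpha 0.05, one NRS unit, SD 2.0, one experimental against one control group, 150 participants, 20% loss allowed for. Two of the three arms do Nordic Walking, and the text does not say which is the experimental group.

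**The concern.** What the article fixes does not fit together. It makes several results primary, yet its alpha and sample size serve only one. That one is on a 0–10 NRS, which is not itself a listed primary score, since the pain index sums six such scales.

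A reader of the finished trial could not tell from this document which result decides the primary question. A significant disability score for A v B and a significant pain index for A v C would each qualify, and the choice could be made after the results are seen. A claim selected in that way has a false-positive rate above 5%. By how much depends on how many primary tests are really meant.

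**Working it through.** **1. What the stated sample size covers**

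Inputs (Data analyses; Study sample): difference 1, SD 2.0, alpha 0.05, power 80%, 50 per arm, 20% loss. Sidedness is not stated; two-sided is assumed first.

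Per-arm size: n = 2(1.960 + 0.842)² × 2.0² / 1² = 62.8, so 63 evaluable.
- Three arms: 3 × 63 = 189; with 20% loss 189 / 0.8 = 236.25, so 237.
- Two arms: 2 × 63 = 126; 126 × 1.2 = 151.2, so 152; or 126 / 0.8 = 157.5, so 158.
- A and B pooled against C, after loss: 180 two-sided, 143 one-sided.
- One-sided pairwise: 50 per arm, 150 in total, with no room for loss.

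The figure of 150 is not reproduced for a pairwise contrast in three arms with 20% loss. The readings that come near it with loss allowed for are a single two-group comparison, or one-sided pooling. On either reading, alpha 0.05 has been spent on one test.

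Power of one pairwise contrast, two-sided, is Φ(1 / (2.0√(2/n)) − 1.96):
- n = 50: Φ(2.500 − 1.960) = 70.5%
- n = 40 (50 less 20%): Φ(2.236 − 1.960) = 60.9%

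**2. Chance of at least one false primary result**

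Assumptions: no true difference, each test two-sided at 0.05, and any one significant result claimable as primary. The three arms were simulated as independent normal vectors (200,000 draws or more), so contrasts share arms as they would in the trial. Pairwise tests use |z| > 1.96; the three-group test uses chi-square on 2 df above 5.99. The documents give no correlations, so a common value between scores, and between times where used, was set at 0 to 0.9.

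| Reading | Tests | corr. 0 | 0.5 | 0.7 | 0.9 |
|---|---|---|---|---|---|
| One three-group test per score, one time | 3 | 14% | 13% | 11% | 8.5% |
| A v B and A v C, three scores, one time | 6 | 25% | 22% | 19% | 15% |
| All three contrasts, scores and times | 27 | 69% | 58% | 46% | 30% |

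Hand check of the first row at correlation 0: 1 − 0.95³ = 14.3%. The formula for fully independent tests gives 1 − 0.95⁶ = 26.5% and 1 − 0.95²⁷ = 75.0% for the other rows. These exceed the simulated 25% and 69% because contrasts that share an arm are not independent.

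**3. Could a later adjustment alone repair this?**

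Bonferroni over three contrasts, for one score at one time (alpha 0.05 / 3 = 0.0167), needs 84 evaluable per arm. With 40 per arm, power is 44%. An adjustment restores the error rate, but 150 participants were not sized for it. A fixed sequence splits no alpha.

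**The case against.** **A condensed article may leave multiplicity to the analysis plan.** This stands. The absence of an adjustment method is no finding, and nothing can be said about the trial's actual error rate. What remains is what the article does state: three scores given equal rank, two wordings of the primary aim, and an alpha and N for one two-group contrast. Those have to be reconciled whatever the plan contains.

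**A reader might infer 27 planned tests and a 75% error rate.** No passage plans 27 tests. Follow-up says only when data are collected, which is compatible with a repeated-measures analysis, and the Background aim is compatible with one three-group test per score. The 75% also requires independence, which shared arms rule out. The leanest reading gives about 8–14%.

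**A reader might infer that there is no primary hypothesis, or that the two aims contradict each other.** Neither is supported. The Abstract states a hypothesis with a direction for pain and function. The Background's comparison includes the Abstract's two contrasts, so one wording is looser than the other. The accurate statement is that no single primary hypothesis is named.

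**The alpha of 0.05 is a sample-size input, not a testing rule.** True. It shows what the trial was sized for and does not prove that every test would be run at 0.05. The inflation figures depend on that assumption and on any one result being enough for a claim.

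**Conclusion.** The concern holds in this limited form: the article makes three scores co-equal primaries over two or three unranked contrasts, with an alpha and a sample size for one NRS contrast whose experimental arm is not identified.

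The false-positive risk is about 8–14% on the leanest reading, about 15–25% on the Abstract's contrasts at one time, and about 30–69% only if every contrast and time is open to a claim. All three ranges rest on assumed correlations and on an assumed rule that one significant result suffices.

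This should be fixed. It is not rated more severely because an analysis plan that is not shown may already hold a multiplicity rule.

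**What to change.** Before unblinding:

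1. **Name one primary outcome as the article defines it**, for example the LBPRS pain index (0–60), and restate the power calculation on that scale. Multiplying by six is not enough: one unit on each scale is 6 points on the sum, but the SD of the sum depends on correlations that are not given. If a 0–10 back-pain NRS is meant, say so explicitly.
2. **Name one primary time**, for example eight weeks.
3. **Fix the sequence at two-sided 0.05:** A v C first, then A v B only if A v C is significant.
4. **Make the rest secondary:** B v C, the other scores and the later times, with estimates and 95% intervals.
5. **If function must stay primary,** name one function score. Apply Holm to pain and function for A v C, and open A v B (again with Holm) only if both are rejected. Opening it after one rejection does not protect the error rate: if pain truly differs for A v C and nothing else does, the familywise error is roughly 7–9% by simulation.
6. **Make the Abstract, Background and Data analyses name the same contrasts** and identify the experimental arm.

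The cost is wording, and some outcomes now called primary lose confirmatory status. The A v C contrast has about 61% power with 40 evaluable per arm and about 71% with 50, under the stated difference of 1 and SD of 2.0. The power statement should say so.

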## Methods

### Design

Singleblinded Radomized Clinical Trial.

### Study sample

The patients are recruited from a secondary sector specialized out-patient back pain clinic. All participants receive information about self-care for back pain and attend group exercises twice a week for four weeks before being offered inclusion into the current project. 50 patients are to be included in each of the three intervention groups, totalling 150 participants.

### Inclusion/exclusion

To be included in the project participants must

• have had LBP with or without leg pain > 8 weeks

• have received four weeks of treatment in the primary sector by a family physician, chiropractor, physical therapist, or a combination thereof

• have ended all examinations, individual and group treatment at the back clinic with at least a 75% attendance rate

• be able to read and understand Danish

Exclusion criteria are

• pain less than 3 on the 11 point numeric rating scale

• co-morbidity preventing patient from participating in the full intervention

• unable to sit on a stationary bike for at least 30 minutes in order to perform watt max bicycle test

### Examination and baseline data

One week after ending the group exercise program, potential participants are assessed in an individual baseline test session. First, they complete a battery of questionnaires including information on social, psychological, occupational, educational, physical and lifestyle factors, expectations to treatment outcome, and baseline values for the outcome measures (see below). Finally, each participant performs a watt max cycle test in order to evaluate their cardiovascular capacity.

### Randomization

Randomization is carried out by a project secretary blinded to the interventions. Participants consenting to participate draw a sealed envelope containing information about treatment allocation. Envelopes are arranged in clusters of 15 to secure an even spread in all groups.

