### Interventions

After test session and randomization, participants are allocated to one of three groups

**Group A **is instructed and performs NW in groups of 6–8 twice a week for 8 weeks under supervision of a specially trained instructor. To monitor the activity level in this group accelerometers are provided for the participants. The participants have to use accelerometers through out the day for 2 weeks (week 4 and 5) during the intervention. In the same period they have to fill out an exercise dairy describing their daily activity.

**Group B **is instructed in NW once by a specially trained instructor, but is afterwards told to perform NW as much as they want to at home on their own for the next 8 weeks. This group also reviews accelerometers and an exercise dairy for 2 weeks (week 4 and 5 during the intervention.

**Group C **is given standard information about exercise and maintaining the daily function level they have achieved during the treatment at the back pain clinic.

NW poles are provided free of charge to everyone included in the project. Participants randomized to group C received their poles after completion of the 8 weeks.

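### One stated cluster size of 15, with arms that are visible once treatment starts, lets anyone tracking allocations deduce the last envelope in every cluster

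*Protocol article*

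**What the plan says.** The Randomization section of the protocol article describes three things:

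- Who runs it: "Randomization is carried out by a project secretary blinded to the interventions".
- How a patient is allocated: "Participants consenting to participate draw a sealed envelope containing information about treatment allocation".
- How balance is kept: "Envelopes are arranged in clusters of 15 to secure an even spread in all groups". No other cluster size is mentioned.

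Study sample sets the target: "50 patients are to be included in each of the three intervention groups, totalling 150 participants".

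Interventions shows that allocation becomes evident after the draw. Group A "performs NW in groups of 6–8 twice a week for 8 weeks under supervision of a specially trained instructor". Group B has one instruction session and then walks alone. Group C is given information, and "Participants randomized to group C received their poles after completion of the 8 weeks".

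**The concern.** A sealed envelope hides its own contents. It does not hide what follows from envelopes already opened. When the block size is constant and known, and each allocation shows itself once treatment begins, a running count reveals what remains in the current cluster. Near the end of a cluster, little or nothing remains uncertain.

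A person who can foresee the next allocation and has a say in who is invited, or when, could match patients to arms. Any resulting difference between the arms arises before allocation, so neither intention-to-treat analysis nor a blinded analyst can undo it. It could distort any outcome, patient-reported or measured.

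The verb used for allocation adds to this. Read literally, the participant picks an envelope and is not given the next one in a fixed order.

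**Working it through.** **Inputs.** Cluster size 15 (Randomization). Three arms of 50, 150 in total (Study sample). Two assumptions: five envelopes per arm in each cluster, inferred from the stated purpose "to secure an even spread in all groups"; and each cluster is used up before the next is opened.

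**The plan's own figure.** 150 / 15 = 10 clusters, and 10 × 5 = 50 per arm. The target is reproduced exactly, which supports the 5/5/5 reading.

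**Draws known with certainty.** Take an observer who knows all earlier allocations and the cluster boundaries. Draw 16 − j is certain when the last j envelopes all belong to one arm:

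P(j) = 3 × (5/15) × (4/14) × … × ((6 − j)/(16 − j))

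| Draw | j | Calculation | Probability |
|---|---|---|---|
| 15th | 1 | 3 × 5/15 | 100% |
| 14th | 2 | previous × 4/14 | 28.6% |
| 13th | 3 | previous × 3/13 | 6.6% |
| 12th | 4 | previous × 2/12 | 1.1% |
| 11th | 5 | previous × 1/11 | 0.1% |

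Expected number of determined draws per cluster: 1 + 0.2857 + 0.0659 + 0.0110 + 0.0010 = 1.36. That is 1.36 / 15 = 9.1%, or 10 × 1.36 = 13.6 of 150 patients.

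**At least one arm ruled out.**

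- Before the 14th draw: always, because two envelopes cannot cover three arms.
- Before the 13th: 1 − 5³/C(15,3) = 1 − 125/455 = 73%.
- Before the 12th: 1 − 3 × C(5,2) × 5 × 5/C(15,4) = 1 − 750/1365 = 45%.
- Average over the cluster, from 200,000 simulated clusters: 3.64 of 15 draws (24%).

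**Best guess.** The observer always names the arm with most envelopes left. With s envelopes left in each arm and t in total, the expected number of correct guesses follows V(s) = max(s)/t + Σ (sᵢ/t) × V(s with one fewer in arm i). This gives V(5,5,5) = 7.46, so 7.46 / 15 = 49.7%, against 33.3% under simple randomization. By position, success rises from 33% at the 1st draw to about 56% at the 12th, 60% at the 13th, 64% at the 14th and 100% at the 15th.

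**Effect of the drawing method.** These probabilities are the same whether participants pick freely from the envelopes left in a cluster or take them in a pre-shuffled order.

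**Would a smaller fixed block help?** No. The same formula gives 1.286 determined draws in a known block of 9 (14.3%) and 1.333 in a known block of 12 (11.1%). Fifteen is already fairly large for three arms. The gain has to come from hiding the boundaries.

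**The case against.** The strongest reply is that the mechanism needs a person whom the article does not describe: someone who knows the cluster boundaries, counts every allocation and influences who enters and when. The envelopes are sealed and the secretary is described as blinded to the interventions. Consent and baseline testing come before the draw. The baseline session is set one week after the exercise programme ends, and several entry criteria are concrete (attendance, pain score, duration of pain). Only the 15th draw is always certain; the 12th to 14th are mostly narrowed.

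Most of this stands and limits the size of the point. It does not remove it. Blinding the secretary does not cover others who see which patients join the walking sessions. Group A walks in groups of 6–8 while a cluster would supply only five such patients, so whoever fills those groups has an ordinary reason to count; that is an inference. The exclusion for co-morbidity that would prevent full participation leaves room for judgement.

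A reader might go further and infer that nothing links an envelope to a participant, or that a redraw would go unnoticed. The article does not support that. It says nothing on numbering, opacity or a log, but it is a condensed account, and such details commonly sit in the full protocol. To draw an envelope may also simply mean taking the next one. Nor does the article show that anyone foresaw or steered an allocation.

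**Conclusion.** The point holds as a modest weakness in the stated allocation method. With a single cluster size and visibly different arms, the final allocation in each cluster can always be deduced by someone with full knowledge of the earlier ones, and those just before it become easier to guess. The worst case is about 9% of allocations fully determined (about 14 of 150) and a best-guess success of about 50% against 33%.

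These limits rest on a 5/5/5 split, clusters used one after another, and perfect tracking throughout. They measure predictability; the article gives no basis for estimating actual bias. The lack of any mention of numbering or a log is a matter to confirm and is not counted as an error.

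**What to change.** - Generate one allocation list by computer, with block sizes that are multiples of three and vary at random. Do not disclose the sizes to anyone who enrols patients.
- Replace drawing with assignment of the next opaque, sequentially numbered envelope, in fixed order.
- Confirm from the full protocol whether envelopes are already numbered and logged, and who enrols patients. If they are, say so in the description.

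The cost is repacking the envelopes. Because recruitment may stop within a block of unknown size, final arm sizes may differ from 50 by a few.
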